## Abstract

**Background:**

Mental health inpatients smoke at higher rates than the general population and are disproportionately affected by tobacco dependence. Despite the advent of smoke free policies within mental health hospitals, limited systems are in place to support a cessation attempt post hospitalisation, and international evidence suggests that most smokers return to pre-admission smoking levels following discharge. This protocol describes a randomised controlled trial that will test the feasibility, acceptability and efficacy of linking inpatient smoking care with ongoing community cessation support for smokers with a mental illness.

**Methods/Design:**

This study will be conducted as a randomised controlled trial. 200 smokers with an acute mental illness will be recruited from a large inpatient mental health facility. Participants will complete a baseline survey and will be randomised to either a multimodal smoking cessation intervention or provided with hospital smoking care only. Randomisation will be stratified by diagnosis (psychotic, non-psychotic). Intervention participants will be provided with a brief motivational interview in the inpatient setting and options of ongoing smoking cessation support post discharge: nicotine replacement therapy (NRT); referral to Quitline; smoking cessation groups; and fortnightly telephone support. Outcome data, including cigarettes smoked per day, quit attempts, and self-reported 7-day point prevalence abstinence (validated by exhaled carbon monoxide), will be collected via blind interview at one week, two months, four months and six months post discharge. Process information will also be collected, including the use of cessation supports and cost of the intervention.

**Discussion:**

This study will provide comprehensive data on the potential of an integrated, multimodal smoking cessation intervention for persons with an acute mental illness, linking inpatient with community cessation support.

**Trial Registration:**

Australian and New Zealand Clinical Trials Registry ANZTCN: ACTRN12609000465257

## Background

Persons with a mental illness are one of the largest remaining groups of smokers, comprising an estimated 32% of the total smokers in Australia [1]. Consistently high rates of smoking have been found among the mentally ill in Australia and internationally, ranging from 36% in community samples to above 90% among inpatients with psychosis [2-5]. Smokers with a mental illness are also more nicotine dependent [6], more likely to smoke unfiltered cigarettes [7] and less likely to quit than smokers in the general population [8-10]. Consequently, smokers with a mental illness have a significantly reduced life expectancy and are more likely to die from smoking related disease including cancers, cardiovascular disease, respiratory disease and stroke [11,12].

Evidence for the effectiveness of multimodal smoking cessation interventions utilising combined pharmacological and psychosocial support is well established for smokers in the general population [13-15]. Recent evidence suggests that smokers with a mental illness have similar levels of motivation to quit as the general population [16-18] and smoking cessation intervention strategies can be equally effective among this group [19-21]. Multimodal smoking cessation interventions have been found to be effective among US veterans with Post-Traumatic Stress Disorder (PTSD) [22], depressed smokers [23], and in smokers with schizophrenia [24].

General hospitals can provide a base for the initiation of effective smoking cessation interventions [25-28]. Abstaining from tobacco during hospitalisation has been associated with higher abstinence rates at 6 months post discharge [29]. The recent introduction of smoke-free policies in Australian mental health facilities [30] provides the opportunity for smokers to temporarily abstain from cigarettes in a supportive environment, and may facilitate sustained cessation attempts upon discharge [2,31]. Hospitalisation within a smoke free mental health facility has been found to increase patients' desire to quit smoking during admission [4,31], and has been associated with a reduction in daily cigarette consumption from admission to discharge [2].

However, the limited data available indicate that smoke-free policies in mental health facilities appear to have had little effect on long term cessation [25], a finding suggested to be due in part to the lack of coordination between inpatient and community smoking cessation treatment [32,33]. Systematic reviews show that by better integrating inpatient smoking care with post discharge cessation support, long term quit rates are increased among general hospital patients [27,28]. However, in the context of mental health services, low levels of smoking cessation treatment have been found in both inpatient and community-based psychiatric services [34-36], and as a consequence, many smokers return to pre admission smoking levels upon discharge from a mental health hospital [4,31,37]. The limited provision of smoking cessation treatment in community-based psychiatric services, to which many patients are likely to be referred upon discharge, highlights the need for integrated post-discharge smoking cessation treatment for smokers with a mental illness [32,33].

Although an Australian randomised control trial of outpatients with psychosis reported that a multimodal smoking cessation intervention was effective in reducing smoking rates [21], the authors are not aware of any published studies that have examined the effectiveness of integrating inpatient smoking cessation care with community cessation support for individuals with a mental illness. This study is the first of its kind internationally to test, via randomised controlled trial, the feasibility, acceptability and efficacy of integrating inpatient smoking care with post discharge ongoing, multimodal smoking cessation treatment for persons with an acute mental illness. This paper describes the methodology to be employed in the conduct of this trial.

## Methods/Design

### Study aim

The aim of this study is to test a multimodal smoking cessation intervention, linking hospital inpatient care (in a smoke free mental health facility) with post-discharge community cessation support for smokers with a mental illness. This study aims to evaluate the feasibility, acceptability and efficacy of the integrated intervention to reduce smoking behaviour and encourage quitting post-discharge. This study will also provide a detailed evaluation of the uptake and use of the study intervention components, including the cost of the intervention.

### Study Design and Setting

This study will employ a single-site prospective randomised controlled study design, and will be reported in accordance with the requirements of the CONSORT statement [38]. It will be conducted at a large regional inpatient mental health facility located in the Hunter New England region of New South Wales (NSW), Australia. Inpatients will be recruited from three units within the facility (two general adult units and one dual diagnosis unit), with a total of 66 beds, with three other units excluded from this study (two emergency psychiatric care units and one geriatric unit). The majority of the study intervention will be delivered in the community setting, upon participants' discharge from hospital and contact between participants and project officers will occur via telephone and mail.

Figure 1 shows the study design. Mental health inpatients who report being current smokers will be approached to participate. Participants will be randomly allocated to intervention or control conditions. A permuted block randomisation approach will be used so that the distribution of participants by diagnosis (psychotic; non-psychotic) across treatment conditions will be maintained regardless of the final sample size [39,40].

**Figure 1 F1:**
[figure not shown]
**Study Design**.

Inpatients allocated to the intervention condition will receive a brief motivational intervention from the research staff, and will be offered a range of psychosocial and/or pharmacological supports for up to 16 weeks post discharge. An initial two week supply of nicotine replacement therapy (NRT) is provided at discharge, and details of the patient's participation in the study will be added to their electronic discharge summary, for the information of health professionals providing post-discharge treatment.

Patients allocated to the control condition will receive standard hospital smoking care only, which may include provision of up to 3 days free NRT and a referral to Quitline upon discharge. Baseline data will be collected during the initial face to face interview in the inpatient setting by trained project officers.

Follow-up outcome data will be collected by blind interviewers independent of the study, via telephone interview at four time points following discharge: one week, two months, four months and six months.

This project has received ethics approval from the Hunter New England Human Research Ethics Committee, HREC reference no: 08/04/16/5.10, and the University of Newcastle Human Research Ethics Committee reference no: H-2008-0191.

### Participants and research eligibility

Approximately 200 smokers will be recruited to the study (100 in each condition). Written, informed consent will be obtained from each potential participant before commencement of the baseline interview.

#### Inclusion criteria

Participants will be required to be at least 18 years of age and to self report being a current or occasional smoker upon admission to hospital. Participants will also be required to have a contact telephone number and address at the time of recruitment, and be judged by clinical staff to be physically and psychologically capable to complete the face to face baseline interview. Any person who presents severe psychological distress during the baseline interview will be referred to clinical staff and the interview will cease. Eligibility will be reassessed after these patients have stabilised.

#### Exclusion criteria

Patients will be excluded if they are not current smokers, are younger than 18 years of age, do not have a current contact telephone number or address, are non English speaking, or if their current physical or mental wellbeing is judged by clinical staff to be too unstable to participate.

### Recruitment and Allocation

Recruitment of participants will be ongoing over, approximately, a one year period. A systematic daily (weekdays only) review of current patients within each unit will be undertaken in conjunction with clinical staff, with advice provided to project staff regarding those patients deemed to be sufficiently stable to be approached on that day. The study will aim to approach all patients at some time during their stay, establishing the smoking status of those patients who agree to speak with project staff. If patients report being a non or ex-smoker, they will be thanked for their time, and the interview will cease. Eligible patients will be offered participation in the project, provided with the information statement about the research, and written informed consent will be obtained. Participants will complete a baseline interview with the project officer (up to 1 hour duration).

#### Allocation

Prior to commencement of recruitment, a random allocation sequence will be generated using SPSS through consultation with an independent statistician not actively involved in the project. The randomisation will follow a permuted block design, restricted to blocks of 10, and stratified by diagnosis (psychotic; non-psychotic) to ensure an even distribution of participants within and between treatment conditions [39,40]. The random allocation sequence will be stored with a research assistant independent of the recruitment process, and all project officers involved in recruitment and follow-up data collection will be kept blind to the sequence. According to the order of the random allocation sequence, the research assistant will place small cards indicating the treatment condition ("Intervention" or "Control") inside sealed, security envelopes, displaying the sequentially ordered participant identification code on the exterior. Following completion of the baseline interview, the project officer will provide the participant with the subsequent envelope in sequence, and the envelope will be opened by the participant at the conclusion of the baseline interview.

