##### b) Brief motivational interview

The project officer will conduct a brief (5-10 minutes) motivational interview by guiding the participant through a series of topics designed to motivate the participant towards positive health behaviour change, including: positives and negatives of smoking and quitting, importance and confidence in quitting, and health and financial costs of smoking [49].

Immediately upon discharge from hospital, intervention participants will receive:

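### A fixed block size of 10 lets up to about one allocation in six be deduced if recruiters know the block size and stratum and pool past allocations, and below 1% if they do not pool

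*Protocol article*

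**What the plan says.** All of this is in the protocol article.

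- **Sequence.** Allocation states: "The randomisation will follow a permuted block design, restricted to blocks of 10, and stratified by diagnosis (psychotic; non-psychotic". No variation in block size is mentioned. Participants and research eligibility gives the ratio: "Approximately 200 smokers will be recruited to the study (100 in each condition".
- **Safeguards.** An independent statistician is consulted on generating the list, and a research assistant outside recruitment holds it. The envelopes are sealed and sequentially coded. Allocation adds that "all project officers involved in recruitment and follow-up data collection will be kept blind to the sequence".
- **Handling of envelopes.** The recruiting officer hands over the next one in order. Opening it is left to the patient: "the envelope will be opened by the participant at the conclusion of the baseline interview".
- **After opening.** For those allocated to intervention, Brief motivational interview says: "The project officer will conduct a brief (5-10 minutes) motivational interview".
- **Setting and staff.** Study Design and Setting describes a "single-site prospective randomised controlled study design". Intervention personnel, recruitment and training names a health psychologist and several project officers as recruiters.
- **Before allocation.** Recruitment and Allocation describes a weekday review of patients with clinical staff, with "advice provided to project staff regarding those patients deemed to be sufficiently stable to be approached on that day". The aim is to approach every patient at some point in the stay.
- **Diagnosis.** Demographic information says that diagnoses are taken from the medical record once the baseline interview is complete.

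**The concern.** Keeping recruiters blind to the list protects future allocations only if they cannot be worked out from past ones. In a block of constant size, once one arm has used its five places, the rest of the block is known to anyone who knows the size and has kept count. Recruiters here learn each arm after the event, and all envelopes are used by one team at one site. The article describes no protection for the block size itself.

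If the next arm can be foreseen, the decision to approach a patient today or tomorrow, or how participation is presented, can depend on it. The arms could then differ at baseline in ways that sealed envelopes do not prevent. This matters more here because recruiters are not blind after allocation and most outcomes start from self-report.

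**Working it through.** The article gives no figure for predictability, so there is none to reproduce.

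**Inputs from the article:** blocks of 10; two strata; 1:1 allocation; about 200 participants; one site. Five of each arm per block is inferred from the 1:1 ratio.

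**Assumptions not in the article:** recruiters know the block size, know the stratum, and either pool all past allocations (upper case) or share nothing (lower case).

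**1. Fixed blocks of 10, full pooling.** Position j is certain if the first j − 1 places already hold all five of one arm. The probability is 2·C(5, j − 6)/C(10, j − 1):

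| Position | Calculation | Probability certain |
|---|---|---|
| 6 | 2 × 1/252 | 0.8% |
| 7 | 2 × 5/210 | 4.8% |
| 8 | 2 × 10/120 | 16.7% |
| 9 | 2 × 10/45 | 44.4% |
| 10 | 2 × 5/10 | 100% |

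The sum is 1.667 per block. This agrees with the closed form 2m/(m + 1) = 10/6 for a block of 2m = 10. The share is 1/(m + 1) = 1/6 = 16.7%, and 200 × 1/6 ≈ 33 participants. In simulation, 95% of trials fall between about 26 and 42. If the strata end in incomplete blocks (for example 95 and 105 participants), the mean is about 32 (15.9%).

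**2. Best guess.** Enumerating all 252 orderings, always guessing the arm that is behind in the block is right 65.3% of the time, against 50% by chance.

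**3. Fixed blocks of 10, no pooling.** Each patient is assigned at random to one of k recruiters, and each recruiter counts only their own envelopes. The simulated share certain is 0.5% for k = 2, 0.07% for k = 3 and 0.02% for k = 4.

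**4. Randomly varying blocks, full pooling.** The simulated observer knows the set of sizes but not the order in which they were drawn:

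| Block sizes | Share certain |
|---|---|
| 4, 6, 8 | 2.4% |
| 6, 8, 10 | about 1.5% |
| 8, 10, 12 | 1.3% |
| 6, 8, 10, 12, 14 | about 0.5% |

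For sizes 6 to 14 the best-guess rate is still about 65%. What is removed is certain knowledge; the chance of an informed guess hardly changes.

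**5. A smaller fixed block is worse.** 1/(m + 1) gives 20% for blocks of 8, 25% for 6 and 33% for 4.

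**The case against.** A reader might infer that recruiters see every opened envelope, decide for themselves whom to approach, and so know one allocation in six in advance. The article does not support that.

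- It names several recruiters. It does not say that any one of them sees all envelopes, that allocations are tallied by stratum, or that recruiters are told the block size. The size is printed in the article, but the text does not show whether the article was available during recruitment.
- Diagnosis is taken from the record only after the baseline interview. On the stated procedure, a recruiter need not know which stratum's sequence applies when choosing whom to approach.
- Clinical staff judge who is stable enough, and the study aims to approach all patients. Consent and the baseline interview come before the envelope is opened.
- Independent generation, an independent holder and sealed sequential envelopes are recognised safeguards, and 10 is a fairly large block.

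These points stand. They make one in six an upper figure and narrow the route to bias. They do not close it. A single-site team in regular contact can easily pool what it knows. Daily work with clinical staff may reveal a diagnosis earlier. The timing and manner of approach and consent remain open to influence. Nor is this a detail that the article left to a fuller document: the constant block size is a stated design rule.

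**Conclusion.** The weakness is real but moderate. With a fixed 5:5 block of 10, up to about one allocation in six (about 33 of 200) can be deduced in advance. That requires recruiters to know the block size and the patient's stratum and to pool all past allocations. Without pooling, the share is below 1%. The article does not show where between these limits the trial lies.

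It would go too far to say that allocation concealment fails, since the documents show only that it can be incomplete towards the end of a block. The remaining opening is mainly when and how a patient is approached and asked for consent. Nothing in the article is miscalculated or contradictory here. The case for change is that an avoidable route to selection bias can be nearly closed at almost no cost.

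**What to change.** Have the independent statistician generate the sequence within each diagnosis stratum with block sizes drawn at random, for example from 6, 8, 10, 12 and 14. If recruitment has begun, apply this to unused envelopes only. Withhold the sizes from recruiting staff and from public documents until recruitment closes, and say in the protocol that this is done.

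The cost is one regenerated list and its envelopes, with no extra patients or recruiting staff. The largest possible end-of-trial difference between arms rises slightly. An unfinished block of 10 can leave a stratum at most 5 apart, and an unfinished block of 14 at most 7 apart. Over two strata that is at most 10 against 14 among 200, and usually far less.

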### Intervention condition

In addition to hospital smoking care, the participants randomised to the intervention condition will be provided with a 'base' intervention component, comprising a brief motivational interview and smoking cessation self-help material in the inpatient setting. Participants will also be offered the following 'additional' components of the intervention, to occur post discharge: up to 12 weeks of ongoing NRT; a proactive Quitline referral; and a referral to community smoking cessation support groups. Upon discharge, participants will receive an initial two week supply of NRT, and their participation in the study will be recorded on the hospital discharge summary and sent to relevant treating practitioners in the community. Participants will additionally receive supportive phone contact at three days, and one week post hospitalisation, and the delivery of the elected intervention components will commence. Subsequently, participants electing any of the 'additional' intervention components will concurrently receive up to 16 weeks of further fortnightly telephone support.

#### Intervention content

The smoking cessation intervention focuses on the adoption of multiple, evidence based cessation strategies to assist with smoking reduction and abstinence, at the participant's discretion [14,15]. Quitting smoking will be the focus of the intervention. However, a harm minimisation approach will also be employed, through encouraging a reduction in the number of cigarettes smoked per day [41-44]. At the completion of the baseline interview, and following allocation to the intervention condition, participants will receive:

#### 'Base' Intervention component

##### a) Smoking cessation self-help material

Participants will be provided with a clear, plastic folder containing a pamphlet and workbook targeted at smokers with a mental illness developed by a state government provided, proactive telephone smoking cessation support service 'Quitline' [45,46], a smoking and mental health factsheet developed by a national mental health charity organisation 'SANE' [47], and a one page document (developed by the research team) with instructions on how to effectively use NRT, and how to manage nicotine withdrawals and NRT side effects [48].

##### b) Brief motivational interview

The project officer will conduct a brief (5-10 minutes) motivational interview by guiding the participant through a series of topics designed to motivate the participant towards positive health behaviour change, including: positives and negatives of smoking and quitting, importance and confidence in quitting, and health and financial costs of smoking [49].

Immediately upon discharge from hospital, intervention participants will receive:

##### c) Initial NRT supply

To allow for continuation of inpatient and community smoking cessation treatment, an initial two week supply of NRT will be provided to the patient at discharge. Subsequent NRT supplies are delivered in the community setting (below).

